# The Smartphone Peer Physical Activity Counseling (SPPAC) Program for Manual Wheelchair Users: Protocol of a Pilot Randomized Controlled Trial

**DOI:** 10.2196/resprot.7280

**Published:** 2017-04-26

**Keywords:** Manual wheelchair, Physical activity, Peer training, Smartphone, Randomized controlled trial

## Abstract

**Background:**

Physical activity (PA) must be performed regularly to accrue health benefits. However, the majority of manual wheelchair users do not meet PA recommendations. Existing community-based PA programs for manual wheelchair users appear to work, but effect sizes are small and retention is low. Existing PA programs may not fully implement some psychosocial factors that are strongly linked with PA (eg, autonomy). The use of peers and mobile phone technology in the Smartphone Peer PA Counseling (SPPAC) program represents a novel approach to cultivating a PA-supportive environment for manual wheelchair users.

**Objective:**

The primary objective is to compare change in objective PA between the experimental (SPPAC) and control groups from baseline to postintervention (10 weeks) and follow-up (3 months). Changes in and relationships between subjective PA, wheelchair skills, motivation, self-efficacy (for overcoming barriers to PA for manual wheelchair use), satisfaction of psychological needs for PA, and satisfaction with PA participation will be explored (secondary outcome). Program implementation will be explored (tertiary objective).

**Methods:**

A total of 38 community-living manual wheelchair users (≥18 years) will be recruited in a randomized controlled trial (RCT). Participants in both the control and experimental groups will receive existing PA guidelines. Participants in the experimental group will also receive the SPPAC program: 14 sessions (~30 min) over a 10-week period delivered by a peer trainer using a mobile phone. PA activities will be based on individuals’ preferences and goals. Implementation of important theoretical variables will be enforced through a peer-trainer checklist. Outcomes for objective PA (primary) and subjective PA, wheelchair skills, motivation, self-efficacy, satisfaction of psychological needs, and satisfaction with participation will be collected at three time points (baseline, postintervention, follow-up). Multiple imputations will be used to treat missing data. A mixed-model ANCOVA will be conducted, controlling for covariates (primary and secondary objectives). The strength and direction of the relationships between the primary and secondary outcomes will be explored (secondary objective). Descriptive and content analysis will be used to appraise program implementation (tertiary objective).

**Conclusions:**

There may be substantial benefits for the SPPAC program including limited burden on health care professionals, decreased barriers (eg. accessibility, transportation), development of peer social supports, and potential cost savings related to physical inactivity. Before conducting a large and expensive multisite RCT within a small heterogeneous population of manual wheelchair users, a pilot study affords a prudent step to establishing an adequate study protocol and implementation strategies.

**Trial Registration:**

ClinicalTrials.gov NCT02826707; https://clinicaltrials.gov/ct2/show/NCT02826707 (Archived by WebCite at http://www.webcitation.org/6pqIc14dU)

## Introduction

Despite numerous physical (eg, functioning), psychological (eg, quality of life), and social (eg, inclusion) benefits of physical activity (PA) [1], more than 55% of adults (18-74 years) and 90% of older adults (≥60 years) who use wheelchairs are not physically active enough to accrue health benefits [2,3]. The sedentary nature of sitting in a wheelchair can trigger a chain of negative physiological and psychological events that can exacerbate physical, psychosocial, and mental sequelae overtime [4]. Therefore, the health benefits of PA may be amplified for manual wheelchair users [5,6]. For instance, even moderate amounts of PA could optimize functioning and slow the spiraling effects of deconditioning that are associated with disability [7].

Compared to the general adult population, manual wheelchair users face additional barriers to PA participation, including complex health problems [8], lack of accessible spaces, transportation challenges [9], and financial stress [10]. Thus, a need for accessible and affordable PA interventions for manual wheelchair users has been documented [10]. Successful community-based programs have addressed many of these facilitators and barriers for manual wheelchair users using various behavioral approaches (eg, Workout on Wheels [10]), and individuals with spinal cord injury, who account for approximately 80% of manual wheelchair users (eg, Get in Motion [11] and home visits [12]) with variable effects on PA. Two randomized controlled trials (RCTs) of interventions that used health care professionals to prescribe PA (ie, Workout on Wheels and Get in Motion) had small effect sizes on PA [10,11]. Although cofacilitation of a home-based strength-training program by a health care professional and peer trainer had a large effect on PA (ie, strength training), findings of this study are limited by a small sample size and lack of a control group [12].

Existing community-based PA programs have implemented important variables that are known to influence PA (eg, coping, action planning, and self-efficacy). However, participant retention was less than 75% and there was little documentation of PA maintenance over time. One explanation may be that participants in these programs were generally prescribed exercise-type activities (ie, aerobic and strength-training exercises), which may have limited their perceived choice in the activities performed (ie, an important predictor of PA uptake and adherence) [13]. Arguably, improving participation in meaningful activities that require any movement may be considered PA and even small improvements in PA may have a profound impact for manual wheelchair users. Therefore, providing manual wheelchair users with choice in activities represents an important consideration.

Motivations for uptake and maintenance of PA occur through complex psychological processes. Consideration of a multitude of psychosocial variables linked with PA (eg, autonomy, motivation, self-efficacy) is required to elicit large effects on PA that result in sustainable behavior change [14-16]. Self-determination theory provides a framework for cultivating an autonomy-supportive social environment that promotes behavior change through the facilitation of the three basic psychological needs of autonomy (ie, feeling free to choose one’s own behavior), competence (ie, interacting effectively with one’s environment by mastering challenging tasks), and relatedness (ie, feeling meaningfully connected to others within one’s social group) [13-15]. Satisfaction of these basic psychological needs will lead to greater intrinsic motivation [14]. An autonomous supportive environment positively influences behavior change [17], including uptake and adherence to PA [18]. Additionally, self-efficacy (ie, an individual’s situation-specific belief in his or her capability to accomplish a given task or behavior) is one of the most salient factors in predicting uptake and maintenance of PA [16,19,20]. Although perceived competence (from self-determination theory) and self-efficacy are often used interchangeably, a clear distinction between the two concepts has been made [21]. Therefore, distinguishing between competence and self-efficacy may have important implications for better understanding the psychological mechanisms driving changes in PA behavior [21].

The tenets of social cognitive theory provide a useful theoretical lens for incorporating self-efficacy into PA interventions [19,20]. Accordingly, self-efficacy is informed by skill mastery, vicarious experience, verbal persuasion, and reinterpretation of physiological and affective symptoms [16]. Although skill mastery is the most salient of these four sources, interventions that also include vicarious experience have been shown to enhance effects on PA behavior [22]. Therefore, considering integration of theoretical factors from both self-determination and social cognitive theories represents a useful approach to tailor the specific needs of manual wheelchair users for the uptake and maintenance of PA [18].

Targeting the important theoretical factors through strategic program implementation provides one way to cultivate an autonomy-supportive environment that enhances autonomy, motivation, and self-efficacy. First, allowing individuals to choose how they participate in meaningful activities may foster a sense of perceived autonomy, which is important for enjoyment and maintenance of the behavior [13]. Second, interventions led by a peer (ie, a person who has experiential knowledge of a specific behavior and similar characteristics as the target population [23]), can enhance self-efficacy and relatedness through vicarious experiences and shared characteristics. Peers provide an effective context for modeling because they are managing comparable conditions, have experienced similar situations, and are credible [24-26]. Adults try harder and experience higher levels of learning when they learn from individuals who have perceived similarities [27]. Peers have effectively increased PA in both clinical and community settings [12,28-30], and improved manual wheelchair skills in community-living adults [31].

Finally, telephone counseling represents an accessible and affordable approach to PA counseling with promising results for increasing PA among manual wheelchair users [10,11]. Opportunely, mobile phones are becoming ubiquitous and afford greater accessibility and convenience for manual wheelchair users. The use of mobile phones for PA counseling may further target autonomy, motivations, and self-efficacy. For example, the use of mobile phones to deliver a PA intervention offers various methods of contact (eg, voice calls, video calls), which may promote personal choice and autonomy. Video calls would enable face-to-face interactions with a peer, which may further enhance self-efficacy and relatedness through vicarious experience. Additionally, social support created by using existing social apps (eg, Facebook) for communicating with peers and monitoring PA goals may provide an avenue for enhancing motivation and self-efficacy [32,33]. For example, results from a recent RCT showed online social networks comprised of like individuals had larger effects on PA than receiving promotional PA messages from a website, and at a much lower cost [33]. Although the source of motivation that arises through online social networks was unclear, the authors suggested that even minimal exposure to online social cues could have a profound influence on PA [33].

The Smartphone Peer Physical Activity Counseling (SPPAC) program will use the power of peers and technology to foster critical psychosocial constructs as a precursor to PA (ie, autonomy, motivation, self-efficacy) providing a potential solution for delivery of broad-reaching and accessible PA intervention for manual wheelchair users with minimal costs. The proposed study protocol will evaluate the efficacy of the SPPAC program for improving PA in manual wheelchair users through a pilot RCT. Based on changes in PA in the intervention group compared to the control group, the primary objective is to provide effect size estimates of the SPPAC intervention on objective PA from baseline to postintervention (10 weeks) and at follow-up (3 months postintervention). Secondary objectives include exploratory evaluation of changes and relationships in subjective PA, wheelchair skills, motivation, self-efficacy (for overcoming barriers to PA, for manual wheelchair use), satisfaction of psychological needs for PA, and satisfaction with participation in PA. Finally, implementation of the SPPAC program will be examined.

## Methods

### Trial Design

A two-site (Montreal and Quebec City, QC, Canada), single-blind, pilot RCT will be done to evaluate the efficacy of the SPPAC intervention for increasing PA in an experimental group versus a control group. Participants will be randomly assigned to the experimental group (SPPAC) or the control group (existing PA resources for manual wheelchair users) using a 1:1 allocation ratio (Figure 1). A statistician who is not part of the study team will perform randomization procedures using an undisclosed block size that is stratified by site (19 per site).

After consent and enrollment, a research assistant (RA; research professional with at least 2 years experience in clinical research) will collect baseline data and enter it into a secure database. A research coordinator will inform the statistician of enrollment via telephone or email and will obtain group assignment within 48 hours. The research coordinator will then forward the participants’ contact information to a peer trainer (experimental) and will forward PA recommendations to both groups. To reduce the risk of bias, participants will be instructed not to discuss the study with the RAs (two per site), who will be blinded to group allocation. Experimental group participants will complete 14 SPPAC sessions over 10 weeks [34]. Participants in both groups will receive usual care (ie, existing PA resources/recommendations) [35].

**Figure 1 figure1:**
[figure not shown]
Detailed description of the Smartphone Peer Physical Activity Counseling (SPPAC) trial design and outcome assessment. HADS: Hospital Anxiety and Depression Scale, ISEL: Interpersonal Support Evaluation List, BREQ-2: Behavioral Regulation in Exercise Questionnaire-2; LTPA BSE: Leisure-Time Physical Activity Barriers Self-Efficacy scale; LTPAQ: Leisure-Time Physical Activity Questionnaire; PNSES: Psychological Need Satisfaction in Exercise Scale; WheelCon: Wheelchair Use Confidence Scale; WhOM: Wheelchair Outcome Measure; WST: Wheelchair Skills Test.

### Ethics

The protocol for this study was approved by the Research Ethics Boards of the Institut de réadaptation en déficience physique de Québec (IRDPQ). The study protocol was registered (NCT02826707). All study participants will provide informed consent.

### Participants

A total of 38 community-dwelling manual wheelchair users will be recruited on a volunteer basis from three large outpatient rehabilitation hospitals (IRDPQ, Jewish Rehabilitation Hospital [JRH], and Institut de réadaptation Gingras-Lindsay-de-Montréal [IRGLM]) and from two adapted fitness centers (Adaptavie, VioMax). Clinicians at the IRDPQ, JRH, and IRGLM who are part of the researchers’ respective teams will identify potential participants, whereas the fitness centers (Adaptavie, VioMax) will send information to their members by email/mail and word-of-mouth. Collaboration with Adaptavie and VioMax will also facilitate recruitment of peer trainers and may provide an avenue for sustainability of the SPPAC program in the future. Based on our past experiences in recruiting manual wheelchair users, this recruitment strategy is reasonable [1,31,36].

Participants will be between 18 and 65 years [35], live in the community, use a manual wheelchair for mobility, have used a manual wheelchair for 1 month or more, able to self-propel a manual wheelchair for at least 100 m, not be currently meeting the PA guidelines [35], able to communicate in English or French, and cognitively able to engage in the SPPAC intervention. Individuals will be excluded if they have a degenerative condition that is expected to progress quickly (eg, amyotrophic lateral sclerosis). Readiness for PA will be screened using the validated Physical Activity Readiness Questionnaire for Everyone (PAR-Q+) and the electronic Physical Activity Readiness Medical Examination (ePARmed-X+) [37,38].

### Sample Size

Based on variability data (mean, standard deviation) from Nooijen et al [39], 30 participants will be required to detect a 28-minute difference per day in PA between the experimental group and the control group (beta=.20, alpha=.05). A sample size calculation for ANCOVA in RCT designs was performed using G*power [40]. Because Arbour-Nicitopoulos et al [11] reported a 26% dropout rate in a telephone-delivered PA intervention for people living with spinal cord injury, the sample size was increased accordingly (total N=38).

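### At the protocol's own 26% dropout rate, N=38 leaves about 28 participants, not the 30 the sample-size calculation requires

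*Protocol article*

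**What the plan says.** All the relevant figures are in the Sample Size section of the protocol article.

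- Requirement: "30 participants will be required to detect a 28-minute difference per day in PA between the experimental group and the control group", with error rates "beta=.20, alpha=.05", that is, 80% power.
- Method: "A sample size calculation for ANCOVA in RCT designs was performed using G*power". The standard deviation comes from a cited study and is not printed. Sidedness and the number of covariates in the calculation are not stated.
- Dropout: the section cites 26%, observed in an earlier telephone-delivered activity programme for people with spinal cord injury.
- Result: "the sample size was increased accordingly (total N=38").

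The Abstract and the Participants section repeat the total of 38. The Trial Design section gives 1:1 allocation and randomisation "using an undisclosed block size that is stratified by site (19 per site"), which also sums to 38. The article gives no other dropout rate and no other reason for 38.

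**The concern.** A dropout allowance is meant to leave the required number of participants after the expected losses. The losses are a fraction of those enrolled, so the required number has to be divided by the retained fraction. Adding 26% to the required number gives too few, because 26% of the larger enrolled number then leaves.

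At stake is the sample-size claim itself. The article presents 38 as the enrolment that protects 80% power for 28 min/day against 26% dropout. If 38 does not do that, the power claim is slightly too favourable under the article's own assumption. The same slip could also carry over into planning of the larger trial that this pilot is meant to inform.

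**Working it through.** **Inputs, all from Sample Size unless noted**

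- Required participants: 30
- Dropout: 26%, so 74% retained
- Planned total: 38
- Allocation: 1:1 (Trial Design)
- Power 80%, alpha 0.05

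**1. Reproducing the stated total**

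- Required × (1 + dropout): 30 × 1.26 = 37.8, rounded up to 38. By arm: 15 × 1.26 = 18.9, rounded up to 19, and 2 × 19 = 38. This matches the article.
- Required ÷ (1 − dropout): 30 ÷ 0.74 = 40.54, rounded up to 41. By arm: 15 ÷ 0.74 = 20.27, rounded up to 21, so 42 in total. This does not match.

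The first route is an inference, since the article does not show the step. The next two results do not depend on it.

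**2. Expected completers at 26% dropout**

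| Enrolled | × 0.74 | Reaches 30? |
|---|---|---|
| 38 | 28.1 | no |
| 41 | 30.3 | yes |
| 42 | 31.1 | yes |

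**3. Dropout that 38 can absorb**

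(38 − 30) ÷ 38 = 8/38 = 21.1%.

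**4. Effect on power**

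The base figure of 30 cannot be rederived, because the standard deviation is not in the article. Power at 28 therefore has to be bracketed. Assumptions: two-sided 0.05, two groups, one covariate, F test with 1 and N − 3 degrees of freedom, noncentrality f²N.

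- *Lower end: 30 gives exactly 80%.* This requires f = 0.531 (standardised difference d = 2f = 1.06). With the same f, power at N = 28 is 77.0%.
- *Upper end: 30 is the smallest even total that reaches 80%.* Then 28 must fall below 80%. The limiting case is 80% at N = 28, which needs f = 0.551 and gives 82.9% at N = 30.

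Power at 28 completers therefore lies between about 77% and just under 80%.

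**The case against.** **The trial is a pilot.** The Introduction gives the primary objective as providing effect size estimates, and the Discussion looks ahead to a later efficacy trial. Losing two completers barely changes the precision of such estimates. This reduces the consequence but does not remove the inconsistency: the Trial Design section also speaks of evaluating efficacy, and the article chose to justify N by power.

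**The 26% is itself uncertain.** It is borrowed from one earlier trial, and the error is small beside that uncertainty. That is fair, and it is a reason to treat the point as minor. It is nevertheless the only rate the article uses, and the Introduction reports retention below 75% in existing programmes.

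**The analysis may recover some information.** Multiple imputation is planned, and a mixed model can use postintervention data from people who leave before follow-up, so a dropout need not contribute nothing. This stands in part. However, the article does not offer either as the basis for N, and imputation does not in general restore outcome information lost when a participant leaves.

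**Stronger readings that the article does not support**

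- A reader might state as fact that the sponsor multiplied by 1.26. The arithmetic fits, but no formula is shown.
- A reader might quote 77% as the power at 28. That is the lower end of the range in the working and holds only if 30 gives exactly 80%.
- A reader might add a further loss from the 13-hour wear rule in the Primary Outcome Measure section. That rule drops days within a 7-day period, not participants, and the article gives no figure for participants lost through it.

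**Conclusion.** The inconsistency is real and small. The stated requirement, dropout rate and total cannot all hold: at 26% dropout, 38 enrolled leave about 28, roughly two fewer than required. Nothing elsewhere in the article repairs this. The shortfall itself rests only on figures printed in the article.

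The cost is at most about 3 percentage points of power, conditional on the two-sided, one-covariate ANCOVA assumed in the working. The point does not call the validity, conduct or analysis of the trial into question, and it does not show that more participants must be recruited. It is a minor correction to the sample-size justification.

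**What to change.** Keep N=38 and correct the statement in the Sample Size section. It should say that:

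- 38 enrolled retain the required 30 if attrition is no more than about 21%;
- at the cited 26%, about 28 are expected to remain;
- power for 28 min/day is then somewhat below its level at 30, with the figure recomputed by the sponsor from its own G*Power inputs. Until that is done, the range of about 77% to just under 80% should be given with its assumptions, not as a single value.

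This takes a sentence or two, with no extra participants and no change to design or analysis. The downside is a slightly less favourable stated power. If the sponsor would rather keep the claim of 30 completers at 26% dropout, the total has to be 41, or 42 for equal arms. That means three or four more participants, and the totals in the Abstract, Participants and Trial Design sections would have to change to match.

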### Procedure

Outcome measures will be collected at baseline (T1=prerandomization), postintervention (T2=minimum of 2 days and maximum of 10 days), and at 3-month follow-up (T3=retention) (Figure 1). Experimental bias will be minimized by having two trained RAs at each site (one will administer T1 assessments and one will administer T2 and T3 assessments).

### Intervention

According to the Medical Research Council (MRC) framework for developing complex interventions [41], the SPPAC was established through systematic reviews and refined through focus groups and Delphi surveys with experts [34] (Figure 2). A pilot RCT is a pragmatic next step in the MRC framework to evaluate the efficacy of SPPAC for increasing PA and understanding the influence of important theoretical variables for manual wheelchair users (Figure 1).

